#### Experimental procedures

All sessions will be conducted at the same time of day to avoid different responses to changes in circadian rhythm, and the temperature (21–22°C) and humidity (45–60%) of the evaluation areas will be controlled. In the first visit, fasting (4 hours) and resting without exercising in the previous 24 hours will be required. First, participants will be informed about the study’s objectives, sign the informed consent forms, complete the health and lifestyle questionnaires, and the inclusion and exclusion criteria will be assessed. Subsequently, descriptive data will be collected, and body composition and anthropometric tests will be performed. Finally, blood samples will be collected. Second and third visits will be performed to familiarise the participants with the maximal ramp test on a cycle ergometer and 1-RM exercise to individualise the physical exercise sessions and to familiarise them with the different tests. Subsequent visits will be scheduled according to the timing of the MC phases estimated in the monitoring months. A pre-intervention, immediate post-intervention, 24, 48 and 72-hour post-intervention assessment will be performed at each MC phase (hormone profile). A HITT and strength training session will be performed between the pre-assignment and post-assignment. Table 1 shows the activities to be performed in each MC. This procedure will be performed twice (HIIT and strength training sessions). All outcomes will be assessed by study staff blinded to group assignments as far as possible.

**Table 1 T1:** Study activities

Outcomes	Baseline measurements in each cycle (1 time/cycle)	Baseline measurements in each phase of the MC (3 times/cycle)	Pre-sessions	Post-sessions	24 hours post-sessions	48 hours post-sessions	72 hours post-sessions
Primary outcomes							
Satisfaction			x	x	x	x	x
Visual Analogue Scale for Fatigue (VAS-F)			x	x	x	x	x
Secondary outcomes							
Abdominal obesity and anthropometric variables	x						
Dietary and nutritional monitoring	x						
Monitoring of PA levels	x						
Walking endurance (2-MWT)	x						
Physical self-perception		x					
Catastrophizing Pain Scale		x					
Modified Fatigue Impact Scale		x					
Multiple Sclerosis Quality of Life-54		x					
State anxiety and trait anxiety		x					
Body temperature		x					
Bioimpedance analysis		x					
Reproductive hormonal profile			x				
Inflammatory profiles			x	x*			
Cognitive profiles			x	x*			
Neuromuscular strength, voluntary activation and contractile properties: RFD, MVIC, CAR, MULS			x	x	x	x	x
Functional assessment: spasticity, gait speed, balance, STS, TUG			x	x	x	x	x
Rating of Perceived Exertion			x	x			
Pain: VAS, algometer			x	x	x	x	x
Muscle oxygen saturation			During sessions				
Lactate			x	x†			
VO_2_max			During sessions				
Heart rate variability (HRV)			During sessions				
Quality of sleep: Karolinska Sleep Diary Questionnaire, actigraphy-based sleep quality, HRV					x	x	x

*It will be assessed immediately, at 30 min and 2 hours after the end of the session.

†It will be assessed immediately, at 3 min and 30 min after test.

CAR, central activation ratio; MC, menstrual cycle; MULS, maximal upper limb strength; MVIC, maximal voluntary isometric strength of the lower limbs; 2-MWT, 2-Minute Walk Test; PA, physical activity; RFD, rate force development; STS, sit-to-stand; TUG, timed up and go test; VO_2_max, maximal oxygen consumption.

### Exercise training sessions

The characteristics of each HIIT and strength training session that participants will perform have been designed according to the recommendations provided by guidelines^31^ and results reported in recent meta-analyses published by Andreu-Caravaca *et al*^15 16^ and Campbell *et al*,^14^ to optimise the long-term results of physical exercise programmes.

#### HIIT session protocol

The proposed protocol for the HIIT session is based on previous studies conducted with this population on a cycle ergometer, with the following distribution: 5 min of warm-up at 50% of peak power+20 min of HIIT consisting of 30 s at 90% of peak power, followed by 30 s of passive rest+5 min of cool-down at 35–40% of peak power. Participants will be asked to maintain a cadence between 50 and 80 revolutions per minute (rpm); if participants do not achieve 50 rpm, they will be encouraged to cycle as fast as they can (but not less than 40 rpm). Peak power will be previously determined through an incremental cycle ergometer test using the cycle ergometer (Ergoselect 200, Ergoline, Germany), which will include 5 min of warm-up with unloaded cycling followed by a ramp incremental test with 25 W increments every 2 min until exhaustion. The test will be terminated when the participants reach volitional exhaustion or the cadence drops by 10 rpm.^25 32^ During the test and the sessions, the heart rate will be measured by an H10 heart rate monitor (Polar Electro, Kempele, Finland), and the cardiorespiratory response will be analysed using a gas analyser VO2 Master Pro (VO2 Master Health Sensors, Vernon, British Columbia, Canada). Peak power will also be established during each of the MC phases. Peak power will serve as a baseline at each of the hormone phases.

#### Strength training session protocol

Participants will perform a standardised warm-up protocol (5 min on a stationary bicycle, mobility of the lower extremities and 5 repetitions at 40% 1-RM on each machine) before each strength training session. Subsequently, participants will perform four lower limb exercises, including bilateral leg press, unilateral leg extension, unilateral hip extension and bilateral seated calf raise on conventional weight machines (Fittech, Viseu, Portugal). The session’s intensity will be 70–75% of 1-RM, performing a volume of 4 sets of 10 repetitions, leaving 1–2 repetitions in reserve (RIRs) and 120-second rest between sets. The 1-RM will be calculated for each exercise in the familiarisation phase.

The 1-RM load will be estimated using the following protocol: 1 set of 10 repetitions at 50% of the estimated 1-RM, 1 set of 5 repetitions at 75% of the estimated 1-RM, finishing with 1 set of 1 repetition at 100% of 1-RM. A 5-minute rest period will be allowed between sets. If a participant can complete more than one repetition in the last set, the 1-RM will be estimated based on recommendations published in the literature. Supervisors will instruct participants to lower the weight in a controlled manner, pause briefly at the end of the movement and then contract the muscle as fast as possible (concentric phase) to maximise the neural component. In the training session, the load will be increased by 2–5% when the participants can achieve two more repetitions than the predetermined ones, always with two RIRs.

During the session, the supervisors will fill out a control sheet where the weight lifted in each exercise, the completed repetitions and sets, and RIR will be recorded. All sessions will be supervised by the same certified trainer, specialised in strength training. The 1-RM will be established during the control phases of the MC, and a baseline will be set at different points in the hormonal phase for the study.

### Outcome measures

All outcomes will be conducted and interpreted by study personnel who are blinded to group allocation (table 1).

#### Primary outcomes

##### Satisfaction

Satisfaction with PA will be assessed using an eight-item scale adapted from previous studies.^33 34^ The questionnaire begins with the statement ‘When I am doing PA’, followed by the items ‘I am satisfied with the results of/I am satisfied with/I enjoy/I feel good when I have done/I notice positive results if I have done PA’, ‘PA has many advantages’ and ‘I find PA nice/difficult’. Responses to this single-item question will be measured on a 5-point Likert scale, ranging from 1 (very dissatisfied) to 5 (very satisfied). Satisfaction will be assessed before, immediately following the training session, and at 24, 48 and 72 hours.

##### Visual Analogue Scale for Fatigue

Visual Analogue Scale for Fatigue (VAS-F): to measure fatigue, the VAS-F will be used. The VAS-F will be assessed before, immediately following the training session, and at 24, 48 and 72 hours. This scale, developed by Lee *et al*,^35^ is subdivided into two subscales: fatigue and energy. The VAS-F presents a horizontal line measuring 100 mm in length, with the term ‘none’ at one end and ‘very severe’ at the opposite end. Participants must mark the point on the line corresponding to their perception of fatigue severity between these two endpoints. The fatigue subscale is organised, from the most positive to negative items. Conversely, the energy subscale ranges from the most negative to the most positive items. A high score on the VAS-F indicates a low score on the energy subscale and a high severity level on the fatigue subscale.^36^ This scale is widely used in the general population and clinical patients due to its brevity, ease of use and comprehensibility. The fatigue subscale of the VAS-F shows a Cronbach’s α of internal consistency of 0.90. The Cronbach’s α for the energy subscale is 0.74. Participants will be instructed to consider their overall level of fatigue when responding to the scale rather than a specific moment.

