Thus, the objectives of the study are: (a) to identify moderating variables that modify satisfaction with HIIT and strength training sessions throughout the MC in females with and without MS, and (b) to compare the acute effects of different types of PA sessions (HIIT and strength training) throughout the MC, in females with and without MS.

The central hypotheses of this study are the following: first, during the luteal phase of the MC, females with MS are expected to show a stronger association between inflammation and perception (fatigue and energy) and hormonal levels, as compared with females without the disease. Furthermore, HIIT and strength training sessions are expected to impact satisfaction with PA practice in both populations throughout the MC. During the luteal phase of the MC, females with MS are expected to exhibit different acute responses to HIIT and strength training sessions as compared with females without the disease.

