## Material and methods

### Design

The present protocol describes the methodology of the EMMA Study, a randomised, single-blind crossover trial conducted on females with MS, matched 1:1 based on age, lifestyle factors (smoking, PA) and country of residence, with females without MS, to analyse the effect of PA practice (HIIT vs strength training) throughout the MC. To achieve this, the Consolidated Standards of Reporting Trials recommendations and protocols^19^ and previous studies that analysed the impact of the MC in females without MS^20^ will be followed. Participants will visit the facilities approximately 10 times (4 preliminary familiarisation visits and 6 visits to carry out HIIT and strength training session in each phase of the MC) over 3–4 months (figure 1).

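### The VAS-F, a primary outcome, is scheduled around each session to show acute change, but participants are told to rate overall fatigue and not a specific moment

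*Protocol article*

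**What the plan says.** Table 1 of the protocol article lists two primary outcomes, satisfaction and the VAS-F. The VAS-F section fixes the timing: "The VAS-F will be assessed before, immediately following the training session, and at 24, 48 and 72 hours". Experimental procedures gives the same five times: "A pre-intervention, immediate post-intervention, 24, 48 and 72-hour post-intervention assessment will be performed at each MC phase". The Design section plans "6 visits to carry out HIIT and strength training session in each phase of the MC".

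The purpose is set out at the end of the Introduction. Objective (b) is "to compare the acute effects of different types of PA sessions (HIIT and strength training) throughout the MC". One hypothesis is that in the luteal phase "females with MS are expected to exhibit different acute responses to HIIT and strength training sessions", compared with females without the disease. Another expects "a stronger association between inflammation and perception (fatigue and energy) and hormonal levels"; fatigue and energy are the two VAS-F subscales.

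The VAS-F section then closes with the response instruction: "Participants will be instructed to consider their overall level of fatigue when responding to the scale rather than a specific moment". It carries no qualification, and nothing else in the article gives a momentary frame or limits this one to a baseline rating.

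**The concern.** A before-and-after contrast compares two specific moments. The instruction tells the participant to set the moment aside. A woman who follows it has little reason to move her mark between the rating before a session and the one straight after.

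At stake is what a null result on acute fatigue would mean. It could reflect no acute effect, or a question that asked about something else, and the data could not separate the two. If some women follow the instruction and others answer for the moment anyway, the ratings mix two time frames. No analysis can recover a momentary rating that was never requested.

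**Working it through.** **1. The passages side by side.** The article states no figure on this point, so there is none to reproduce. The check is a comparison of text.

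| Element | Where in the article | Time frame implied |
|---|---|---|
| Five ratings per session: pre, immediate post, 24, 48, 72 h | VAS-F section; Experimental procedures; Table 1 | Specific times relative to the session |
| Objective (b) and the hypothesis on acute responses | Introduction | Change following a session |
| Response instruction | VAS-F section, last sentence | Overall, explicitly not a specific moment |

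The third row conflicts with the first two.

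**2. How many ratings are affected.** 5 ratings × 6 sessions = 30 VAS-F ratings per participant, all under the same instruction.

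**3. Where the conflict is sharpest.** The HIIT session protocol gives 5 min warm-up + 20 min intervals + 5 min cool-down = 30 min. The pre and immediate post ratings are separated by little more than that, so an overall rating should barely move. The 24, 48 and 72 h ratings are less clear-cut, because overall has no stated recall period.

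**4. Illustration of what dampening could cost.** Inputs from the Participants section: α = 0.05, target power 0.95, f(V) = 0.80, sphericity correction 0.2. The correction is given as 1/(repetitions − 1), which implies 6 repetitions.

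Assumptions that are not in the article:
- a share w of the acute effect survives the overall wording, with noise unchanged;
- f(V) = 0.80 applies to the VAS-F;
- the test is a two-group repeated-measures F test with noncentrality λ = f²N.

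Formulas: df1 = (6 − 1) × 0.2 = 1; df2 = N − 2; f = 0.80w; power = P(noncentral F > F at 0.95).

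Sample sizes: the abstract gives 30 in total and the Participants section gives 60, with at least 15 per group. Taking off the stated 25% dropout gives 30 × 0.75 = 22.5, taken as 22, and 60 × 0.75 = 45. Dropout was already considered in the stated estimate, so 22 and 45 apply only if 30 and 60 are numbers recruited.

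Worked case, w = 0.5 and N = 30: f = 0.40; λ = 0.16 × 30 = 4.8; df = 1, 28; critical F = 4.196; power = 0.562.

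| Share retained (f) | N = 22 | N = 30 | N = 45 | N = 60 |
|---|---|---|---|---|
| 1.00 (0.80) | 0.946 | 0.988 | 0.999 | 1.000 |
| 0.75 (0.60) | 0.763 | 0.887 | 0.976 | 0.995 |
| 0.50 (0.40) | 0.431 | 0.562 | 0.746 | 0.861 |
| 0.25 (0.20) | 0.145 | 0.185 | 0.259 | 0.332 |

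A slightly more conservative noncentrality convention gives 0.53 at N = 30 and 0.85 at N = 60 for half the effect, so the picture does not turn on that choice.

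**The case against.** The strongest reply is that overall need not mean habitual. No recall period is given, so a participant might read it as today, or as the time since the last rating, and the 24, 48 and 72 h ratings could still change. This stands, and it is why the conclusion is likely dampening, clearest for pre versus immediate post, and not removal of the effect.

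Overall might instead mean whole-body as opposed to local fatigue. That reading fails, because the sentence contrasts overall with a specific moment, which is a contrast of time. Nor can the sentence be put down to condensing for a journal or to an unseen analysis plan: it is a positive instruction, and an analysis plan does not set how a question is put to participants.

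The objection to the power figures largely stands. The retained share is nowhere in the article. The Participants section ties planning to a study of hormonal differences, so f(V) = 0.80 was not derived for fatigue ratings. The two stated sample sizes lead to quite different losses.

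Three stronger readings are tempting and not supported:
- **That responsiveness to cycle phase is also lost.** Phases lie days to weeks apart, and an overall rating could differ between them. The hypothesis on the association of perceived fatigue and energy with hormone levels does not need a before-to-after change.
- **That the overall frame adds nothing because the Modified Fatigue Impact Scale already captures habitual fatigue.** The article names that scale and its timing, but gives neither its content nor its recall period.
- **That the instruction is shown to suppress the acute effect.** The direction is inferred from the wording; the amount is unknown.

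**Conclusion.** The point holds as an internal contradiction on a primary outcome and should be corrected before data are collected. Confidence is high that schedule and instruction conflict. That the conflict would dampen acute change is a reasonable inference, provided participants do as they are told.

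The size of the loss cannot be derived from the documents. Under the assumptions above, retaining half the effect would leave power between 0.43 and 0.86 depending on which sample size applies; retaining three quarters would leave 0.76 to 0.995. These figures show only that the loss could be anything from small to serious. The case for correction rests on the wording conflict, not on them.

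**What to change.** Replace the last sentence of the VAS-F section, and the matching line in the questionnaire, with for example: *At each of the five assessments, participants will be instructed to rate fatigue and energy as they feel right now.*

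If overall fatigue is truly what the investigators want, keep the instruction, state the recall period, and do not use the VAS-F as the primary measure of acute response.

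The cost of the first option is one line of wording, with no extra visits, ratings or participants. The second would also require restating which outcome carries the acute comparison.

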#### Secondary outcomes

Secondary outcomes will be assessed at various time points, with specific protocols outlined in online supplemental material.

10.1136/bmjsem-2023-001797.supp1Supplementary data

##### Baseline outcomes measured in each MC (control outcomes)

Baseline assessments will be conducted in each MC, including evaluations of abdominal obesity and anthropometric variables, dietary and nutritional monitoring, monitoring of PA levels and walking endurance.

##### Measurements in each phase of the MC

Throughout different phases of the MC, various measurements will be carried out. These assessments include the evaluation of physical self-perception, assessment using the Catastrophizing Pain Scale, analysis of the Modified Fatigue Impact Scale, examination of the Multiple Sclerosis Quality of Life-54, evaluation of state anxiety and trait anxiety, monitoring of body temperature and bioimpedance analysis.

##### Assessments before and after each physical exercise training session

Before and after each physical exercise training session, the following evaluations will take place: measurement of reproductive hormones, including 17β-oestradiol, progesterone, prolactin, LH, follicle-stimulating hormone, thyroid-stimulating hormone and testosterone; analysis of inflammatory markers, such as interleukin (IL)-6 and IL-10; assessment of cognitive function, including brain-derived neurotrophic factor; examination of the blood profile; evaluation of neuromuscular strength, voluntary activation and contractile properties, including rate force development, maximal voluntary isometric strength of lower limbs, muscle contractile function and central activation ratio; and analysis of maximal upper limb strength. Functional assessment includes evaluating spasticity, gait speed, balance, the sit-to-stand test, the timed up and go test, pain levels and the rating of perceived exertion.

##### Evaluations during intervention sessions (per session)

During each intervention session, the following evaluations will be conducted: measurement of muscle oxygen saturation, analysis of lactate levels, assessment of VO_2_max and monitoring of heart rate variability (HRV).

##### Assessing residual effects of exercise training sessions

Sleep quality will be evaluated over the three nights following each intervention to assess the lingering effects of exercise training sessions. This assessment will use the Subjective Sleep Quality Questionnaire, sleep quality measured by actigraphy and HRV.

## Data Availability

No data are available. All data relevant to the study are included in the article or uploaded as online supplemental information.
